#### Endometrial biopsy

Participants randomised to the intervention arm of the PIP studies will undergo an endometrial biopsy procedure, performed using a biopsy catheter (for example, Pipelle de Cornier, Laboratoire CCD, France).

Unless otherwise requested, the woman will lie in the dorsal or lithotomy position and a speculum will be inserted into the vagina. The biopsy catheter will be inserted through the cervix up to the fundus. A tenaculum may be placed on the anterior lip of the cervix to help straighten the internal os to aid delivery. The internal piston is withdrawn to create negative pressure. The catheter is advanced to the fundus and then moved back and forth four times, rotating 90 degrees each time, to collect the biopsy (Fig. 1). The catheter is then removed followed by the speculum. The catheter containing the biopsy sample is then discarded unless the endometrial sample is required for another purpose.

**Fig. 1 Fig1:**
[figure not shown]
The endometrial biopsy procedure. Image provided by Krames Staywell, [name], [contact])

If the pipelle is unable to be inserted into the uterus, local anaesthetic and cervical dilation are permitted, or a second attempt may be scheduled. The procedure is to be abandoned at the participants’ request — for example, due to pain or discomfort — or if the operator is unable to pass the pipelle. These participants will be retained in the group denominator as per intention-to-treat principles.

#### Placebo procedure

In PIP-PCOS and PIP-UE, women in the control arm of the trial will undergo a placebo procedure which is designed to blind participants to their allocation. If couples who are attempting to conceive with sexual intercourse are aware of their study allocation, they may purposely or inadvertently influence their pregnancy outcome through behavioural changes, such as a change in sexual frequency or timing.

For the placebo procedure the women will lie in the dorsal or lithotomy position and a speculum will be inserted into the vagina. The biopsy catheter will be placed at the posterior fornix but not inserted into the external os of the cervix. The internal piston is withdrawn and the catheter moved and rotated slightly to replicate the standard biopsy action. The catheter is then removed, followed by the speculum. The catheter is then discarded.

Participants randomised to the control group in PIP-IVF will not undergo any procedure that is additional to standard care.

Shortly following the procedure and before leaving the clinic, participants will be asked to record the pain they experienced during the procedure on a 10 cm VAS. Participants will also be handed an information leaflet detailing what to expect following an endometrial biopsy, and told to seek medical attention and contact the study coordinator if they experience any adverse events that are potentially associated with the procedure, for example, heavy bleeding or signs of infection such as foul smelling discharge.

In PIP-IVF, participants will be contacted within one week of the procedure and asked to report whether they had any vaginal bleeding the day following the procedure. Women in PIP-PCOS and PIP-UE will be asked to complete a study diary for the three study cycles. In this diary they will record the date of the procedure, whether they had any vaginal bleeding the day following the procedure, each day that they have their period and each time they have sexual intercourse during the on-study period. Women will continue to complete the study diary until their third period following the procedure or until confirmation of a clinical pregnancy (that is, all patients have three cycles or opportunities for conception within the on-study period). Participants should be contacted at least once a month to check in and ensure they are completing the study diary and to provide an opportunity to identify any protocol violations.

### Assessment of participant blinding

The sham procedure employed in PIP-UE and PIP-PCOS is designed to blind participants to their randomisation allocation. The sham procedure involves placing the pipelle in the posterior fornix and not inserting it through the cervix or into the womb, and hence it is expected to cause less pain on average than the interventional procedure. Although participants may not know how much pain to expect from either procedure, some participants may have prior expectations regarding the anticipated degree of pain from either procedure, and this may reduce the efficacy of the blinding. For example, women may have had previous intrauterine procedures or read information about endometrial biopsy on the Internet.

To assess whether participants in PIP-PCOS and PIP-UE are truly blinded to their study allocation, they will be asked to guess their study allocation (from the options of: pipelle procedure, placebo procedure or don’t know) and to supply a reason to support their guess. Participants will be randomised a second time following the procedure to either the ‘ask early’ group or the ‘ask late’ group. The ‘ask early’ group will be asked to guess their allocation within one week of the procedure, and the ‘ask late’ group will be asked to guess their allocation at the end of the study (that is, when the participant knows whether or not they have fallen pregnant in the study). Participants randomised to early will also be asked to guess again at the end of the study, to assess whether there are changes in response over time. Participants will be informed of their allocation after they guess their allocation at the end of the study.

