### Blinding

PIP-IVF is an open label study; women will be aware of their study allocation as they will be randomised to undergo either endometrial biopsy or no procedure.

PIP-PCOS and PIP-UE are single-blind studies; women will not be aware of their study allocations as they will be randomised to either an endometrial biopsy or a sham procedure (placement of the pipelle in the anterior fornix).

In all three studies, the doctor performing the procedure will necessarily be aware of the participant’s allocation.

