### Outcomes

The primary outcome is live birth rate per woman randomised, as defined previously [35].

Secondary outcomes include:ongoing pregnancy per woman randomised (defined as continuing pregnancy diagnosed by ultrasonographic visualisation of one or more gestational sacs on or after 12 weeks gestation)clinical pregnancy per women randomised (defined as a pregnancy diagnosed by ultrasonographic visualisation of one or more gestational sacs, including ectopic pregnancy)biochemical pregnancy (defined as βhcg > 25 mIU/ml) PIP-IVF onlymultiple pregnancies per women randomised and per clinical pregnancy (defined as ultrasonographic visualisation of two or more gestational sacs or heartbeats)ectopic pregnancy per women randomised and per clinical pregnancy (defined as a pregnancy in which implantation takes place outside the uterine cavity)miscarriage per women randomised and per clinical pregnancy (defined as the spontaneous loss of a clinical pregnancy before 20 completed weeks of gestational age)neonatal characteristics (for example, gender, gestation at birth, malformations)placenta characteristics (placenta previa: major, placenta previa: minor, placental abruption, placenta accreta: previous uterine surgery, placenta accreta: no previous uterine surgery)pain during the procedure (as measured by a 10 cm visual analogue scale (VAS))bleeding the day following the procedure.

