##### PIP-PCOS and PIP-UE

Participants in PIP-UE and PCOS are asked to try to conceive for three cycles: the cycle in which they undergo the study procedure and the two following cycles. Participants remain in the study until they either achieve a clinical pregnancy or get their third menstrual period following the procedure. This means that each participant has three cycles whilst on the study where they have the opportunity to conceive. For PIP-PCOS women this time frame is constant regardless of whether the cycles are ovulatory or not. The three study cycles are defined as the on-study period (Fig. 3).

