### Follow-up

The first clinical outcome assessment (clinical pregnancy) will be done via ultrasound at approximately six weeks gestation at the respective trial centres. Ongoing pregnancy will then be assessed via ultrasound on or after 12 weeks gestation. Live birth is the primary study outcome and will be determined via correspondence with participants, from hospital records or via outcome data collected retrospectively at the trial centres.

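### In PIP-UE and PIP-PCOS, women who conceive are told their allocation before live birth is ascertained, and the single-blind label does not state this limit

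*Protocol article*

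**What the plan says.** The Blinding section of the protocol article says: "PIP-PCOS and PIP-UE are single-blind studies; women will not be aware of their study allocations". Table 3 repeats the single-blind label. Neither gives an end point for the blinding.

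The section Assessment of participant blinding sets that end point: "Participants will be informed of their allocation after they guess their allocation at the end of the study". It explains the timing of the late guess as "at the end of the study (that is, when the participant knows whether or not they have fallen pregnant in the study". The on-study period for these two trials ends at the same stage: "Participants remain in the study until they either achieve a clinical pregnancy or get their third menstrual period following the procedure".

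The primary outcome comes later. Under Outcomes: "The primary outcome is live birth rate per woman randomised". Under Follow-up, live birth "will be determined via correspondence with participants, from hospital records or via outcome data collected retrospectively at the trial centres". The Statistical analysis section scores a woman without live birth data as not having had one. The Participant withdrawal section stops all data collection from the moment a woman withdraws.

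**The concern.** Only women who conceive can have the primary event, and they are the women whose follow-up continues after disclosure. From then until birth they know whether they had the biopsy or the sham. A woman told she had the sham might be less inclined to answer a letter months later, or might withdraw. If that happened more in one arm than in the other, the rule for missing outcomes would turn it into an apparent difference in live birth. Withdrawal matters more than silence, because hospital records can replace an unanswered letter but may not be collected once a woman has withdrawn.

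The Background of the article itself names inadequate blinding and high attrition among the weaknesses that exaggerated effects in earlier trials. A reader who sees the single-blind label in the Blinding section or Table 3 could take it to extend to the primary outcome.

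**Working it through.** **1. Order of events for a woman who conceives**

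| Event | Where stated | Timing |
|---|---|---|
| Three conception cycles | On-study period | before disclosure |
| Clinical pregnancy by ultrasound | Outcomes; Follow-up | about 6 weeks gestation |
| Final guess, then disclosure | Assessment of participant blinding | once pregnancy status is known |
| Ongoing pregnancy | Outcomes; Table 2 | 12 weeks or later |
| Live birth | Outcomes; Table 2 | birth |

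Table 2 gives the end of the study its own column, ahead of the 12-week and birth columns. Taking birth near 40 weeks (assumption), 40 − 6 = 34 weeks, or roughly 7 to 8 months, pass between the first scan and birth.

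**2. The protocol's PIP-UE rates reproduce**

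Inputs from Sample size, PIP-UE: 3% and 9% pregnancy per cycle, three cycles, live birth 19% lower than pregnancy.

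- Pregnancy: 1 − 0.91³ = 24.6% and 1 − 0.97³ = 8.7%, stated as 25% and 9%.
- Live birth: 24.6% × 0.81 = 20.0% and 8.7% × 0.81 = 7.1%, stated as 20% and 7%.
- Design difference: 20 − 7 = 13 percentage points.

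**3. How many women are exposed**

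PIP-UE plans 350 women at 1:1, so 175 per arm.

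- Biopsy: 175 × 0.25 = 43.75, about 44 pregnancies. Expected losses before birth: 43.75 × 0.19 = 8.3.
- Sham: 175 × 0.09 = 15.75, about 16 pregnancies. Expected losses before birth: 15.75 × 0.19 = 3.0.
- Share not conceiving on study, whose outcome is settled when they are told: 75% and 91%, or 1 − (0.25 + 0.09)/2 = 83% overall.

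The PIP-PCOS sample size is built on live birth rates and gives no pregnancy rate, so the same count cannot be made there from the document.

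**4. Illustration of the bias**

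Assumptions: no true effect; 9% pregnancy in both arms; live birth rate 0.09 × 0.81 = 7.29% (12.8 births per arm); a fraction m of sham-arm live births unascertained and scored as none; none missed in the biopsy arm. Then the spurious risk ratio is 1/(1 − m) and the spurious difference is 7.29% × m.

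| m | Sham births missed | Spurious difference | Spurious risk ratio |
|---|---|---|---|
| 5% | 0.6 | 0.4 points | 1.05 |
| 10% | 1.3 | 0.7 points | 1.11 |
| 20% | 2.6 | 1.5 points | 1.25 |

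If the births were missed in the biopsy arm instead, the risk ratio would be 1 − m: 0.95, 0.90 or 0.80. The document gives no value for m and no direction.

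**The case against.** The strongest answer is that the sham does what the protocol says it is for. The Placebo procedure section justifies it as a guard against couples changing how often or when they have intercourse, and women remain blind throughout the three cycles in which that could matter. For about 83% of PIP-UE women nothing is left to influence when they are told. Live birth is an objective event with three possible sources, so a missed letter does not by itself make an outcome missing. The time of disclosure is stated openly, so the document does not contradict itself. All of this stands, and it keeps the point small.

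Several stronger readings are tempting but unsupported:

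- A reader might infer that the two trials are unblinded for their primary outcome. They are not: conception, the step on which the sham is meant to act, is fully covered.
- A reader might infer from the column order of Table 2 that clinical pregnancy is also assessed after disclosure. The On-study period and Placebo procedure sections keep women on study until a clinical pregnancy is confirmed, so it is probably established by then.
- A reader might expect biased reports of bleeding. The only bleeding outcome concerns the day after the procedure, well before disclosure. The placental outcomes are clinical diagnoses.
- A reader might picture three of about 12 sham births being lost. That is a 25% loss in one arm and none in the other, an extreme case given the record sources.

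The answer does not reach the women who conceive. Their later follow-up is not participant-blind, and withdrawal after disclosure closes the record sources as well.

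**Conclusion.** The point holds in limited form. In PIP-UE and PIP-PCOS, participant blinding ends once pregnancy status is known. For women who conceive, it does not cover ongoing pregnancy, later miscarriage, placental findings or live birth, and the Blinding section and Table 3 do not say so.

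The likely effect is modest. A bias needs three things together: a response or withdrawal pattern that differs by arm after disclosure, failure or closure of the record sources, and the rule that scores missing as no live birth. The document shows no evidence that sham women would respond less. The range in the illustration, a risk ratio of 1.05 to 1.25 or 0.4 to 1.5 percentage points, rests on an assumed one-sided loss of 5% to 20% with no true effect, and is far below the 13-point design difference. It is worth acting on because the bias is avoidable at almost no cost, not because it threatens the trials' main conclusion.

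**What to change.** In Assessment of participant blinding, keep the guess where it is. Tell women who finish the three cycles without a pregnancy their allocation then, as planned. For women with a pregnancy, disclose only after its outcome, live birth or loss, has been recorded.

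If disclosure is not delayed, state in the Blinding section, and in Table 3, that participant blinding covers the conception period only.

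The cost is a change of wording and of the timing of one communication. Women with a pregnancy wait longer to learn their allocation. The sample size, the blinding assessment and the analysis do not change.

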### On-study period (study duration)

#### ᅟ

##### PIP-IVF

Women in PIP-IVF who undergo embryo transfer are usually scheduled for a serum human chorionic gonadotrophin test to confirm pregnancy approximately two weeks following embryo transfer (Table 1). Women with a positive pregnancy test will be followed up to determine clinical pregnancy by ultrasound at approximately six weeks gestation. The cycle prior to embryo transfer and the embryo transfer cycle are defined as the on-study period (Fig. 2). If the participants’ IVF cycle or embryo transfer is delayed, the recorded outcome will be the pregnancy result of the first embryo transfer which takes place within three calendar months of the expected day one of the embryo transfer cycle/day one of stimulation injections. The expected day one of the embryo transfer cycle is recorded at the time of randomisation.

**Fig. 2 Fig2:**
[figure not shown]
Timing of endometrial injury in PIP-IVF in relation to the IVF cycle and the on-study period. OPU = oocyte pick-up, ET = embryo transfer, hCG = human chorionic gonadotrophin (pregnancy) test

##### PIP-PCOS and PIP-UE

Participants in PIP-UE and PCOS are asked to try to conceive for three cycles: the cycle in which they undergo the study procedure and the two following cycles. Participants remain in the study until they either achieve a clinical pregnancy or get their third menstrual period following the procedure. This means that each participant has three cycles whilst on the study where they have the opportunity to conceive. For PIP-PCOS women this time frame is constant regardless of whether the cycles are ovulatory or not. The three study cycles are defined as the on-study period (Fig. 3).

**Fig. 3 Fig3:**
[figure not shown]
Timing of endometrial injury in PIP-PCOS in relation to the on-study period. hCG = human chorionic gonadotrophin (pregnancy) test

### Follow-up

The first clinical outcome assessment (clinical pregnancy) will be done via ultrasound at approximately six weeks gestation at the respective trial centres. Ongoing pregnancy will then be assessed via ultrasound on or after 12 weeks gestation. Live birth is the primary study outcome and will be determined via correspondence with participants, from hospital records or via outcome data collected retrospectively at the trial centres.

### Statistics

#### Sample size

##### PIP-IVF

Based on the results of a Cochrane review on endometrial injury for IVF, a difference between arms of 16 % may be expected (pooled live birth rates of 33 % and 17 % [43]). At 90 % power and a significance level of 5 % in a two-sided test, at least 188 women are required in each arm (376 in total). In order to power for detection of any subgroup differences (for example, whether endometrial injury increases live birth rate in women undergoing frozen-thaw transfers) and assuming an equal recruitment of fresh and frozen transfer, the required sample was doubled, raising the total number required to 752.

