## Background

Having a baby is an important goal for many couples. Unfortunately, up to 10 % of couples will not achieve pregnancy after a year of frequent, unprotected intercourse and are defined as being subfertile [1]. Many subfertile couples seek fertility treatments to help them conceive. However, even the most successful fertility treatment, in vitro fertilisation (IVF), has a live birth rate of only 30 % per cycle [2, 3]. Failure of an IVF cycle to result in pregnancy can be due to a number of factors and, even when high quality embryos are replaced, implantation rates remain modest. A lack of adequate endometrial receptivity is thought to be responsible for up to two-thirds of unsuccessful embryo transfers [4].

Endometrial injury is currently being proposed as a technique to improve the endometrial receptivity and in turn the probability of conception in IVF cycles. Endometrial biopsy is the most common procedure used to deliver an endometrial injury [5]. The procedure involves the insertion of a catheter, such as a pipelle sampler, through the cervix and into the uterus, where a sample of the endometrium is obtained via light suction and rotation within the uterine cavity. The biopsy results in a ‘scratch’ or ‘injury’ to the endometrium during the process of obtaining a sample. Outside of the fertility area, pipelle biopsy is routinely performed to collect endometrial samples for diagnostic purposes, for example, in women with abnormal menstrual bleeding. It is a well-tolerated procedure with a proven safety profile [6, 7].

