In 2000 it was first reported in a retrospective study that 11 of 12 women who had undergone a series of investigational endometrial biopsies conceived in their subsequent IVF cycle [8]. A prospective non-randomised study by the same research group reported that women allocated to endometrial biopsy in the cycle prior to IVF cycle were twice as likely to conceive as women who had not [9]. Several studies have since investigated the apparent beneficial effect of endometrial injury in IVF cycles, and although there is substantial heterogeneity in the study designs and participant populations, a recent Cochrane review including randomised controlled trials (RCTs) reports an increase in the probability of pregnancy and live birth following endometrial sampling in the cycle preceding embryo transfer (RR = 1.34, 95 % CI 1.21–1.61 and RR = 1.42, 95 % CI 1.08–1.85, respectively) [5]. Other reviews and meta-analyses which have included both RCTs and non-randomised studies have similar conclusions [10–12]. The effect appears to be the most pronounced in women who have repeatedly failed to achieve a pregnancy after multiple embryo transfers, that is, women with recurrent implantation failure (RIF) [13]. Note that in the only study where endometrial injury was performed on the day of oocyte retrieval, a detrimental effect on pregnancy rate was observed [14].

Almost all of the RCTs assessing endometrial injury are associated with significant limitations that place them at a high risk of bias, which is known to be associated with exaggerated effect estimates (such as lack of adequate blinding and allocation concealment, high rates of participant attrition), or raise questions regarding the generalisability of results (such as use of multiple embryo transfer policies or ovulation induction medications in couples with unexplained infertility, timing of endometrial injury, and the device used for causing endometrial injury). Another common issue in a number of the studies is the potential exposure of the control group to unintentional endometrial injury resulting from a placebo procedure [15–17] or a co-intervention such as hysteroscopy, either prior to study enrolment [18] or simultaneously with the study procedure [19, 20]. Finally, only a small proportion of the studies reported live birth, arguably the most important outcome for both clinicians and subfertile couples.

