### Randomisation

A third-party, Internet-based, data collection and randomisation system will be used to confirm participant eligibility and ensure allocation concealment; that is, participant allocations are concealed within the system until the patient is randomised. Only participants who meet the eligibility criteria can be randomised. In instances where computer or Internet access is not reliable, participants will be randomised using sequentially numbered, opaque, sealed envelopes. Dedicated PIP study personnel will be responsible for randomising participants at each site. Participants will be randomised in a 1:1 ratio using block randomisation of two different sizes between 5–15 repeating in random order, stratified by recruiting clinic and by fresh or frozen-thaw embryo transfer (the latter in PIP-IVF only).

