## Discussion

IVF is the leading treatment for subfertility; however, the success rate remains modest at approximately 30 % per cycle [2, 3]. Endometrial scratching is currently being suggested as a technique to improve the probability of embryo implantation and therefore pregnancy in women undergoing IVF. However, due to the potential for bias associated with many of the available studies, the presence of a therapeutic effect remains uncertain.

The PIP trials are designed to address the gaps in the utility of endometrial scratching as a treatment for subfertility in three different populations. If the beneficial effect of this intervention can be confirmed in these settings, endometrial scratching will provide a cost-effective method for helping women and couples to conceive. On the other hand, if endometrial scratching is found to have no effect, or to be detrimental to the probability of conception, the use of this procedure can be abandoned amongst the clinics and doctors who are recommending this procedure to their patients.

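### PIP-IVF is planned on 17% versus 33% (RR 1.94), unreconciled with the article's own 30% IVF rate and RR of 1.42; on those two figures the fresh and frozen strata have about 72% power, and 188 per arm is the 95%-power number

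*Protocol article*

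**What the plan says.** The PIP-IVF sample size paragraph takes its planning rates from a Cochrane review: "Based on the results of a Cochrane review on endometrial injury for IVF, a difference between arms of" 16% is expected, from "pooled live birth rates of 33 % and 17 % [43"]. It continues: "At 90 % power and a significance level of 5 % in a two-sided test, at least 188 women are required in each arm (376 in total"). To allow for subgroup questions, with frozen-thaw transfer as the example, it goes on: "assuming an equal recruitment of fresh and frozen transfer, the required sample was doubled, raising the total number required to 752". The 10% contingency stated under PIP-PCOS brings this to 840. Under Randomisation, allocation is 1:1 and stratified by clinic and by fresh or frozen-thaw transfer.

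Two other places bear on the planning rates.

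- **Effect.** The Background reports, from a recent Cochrane review carrying a different reference number, "an increase in the probability of pregnancy and live birth following endometrial sampling in the cycle preceding embryo transfer", with a live-birth RR of 1.42 (95% CI 1.08–1.85).
- **Control rate.** The Background says that "even the most successful fertility treatment, in vitro fertilisation (IVF), has a live birth rate of only" 30% per cycle. The Discussion says that "the success rate remains modest at approximately" 30% per cycle.

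**The concern.** The planned effect, 33/17, is a risk ratio of 1.94. That is above the upper confidence limit (1.85) of the live-birth effect cited in the Background for the same intervention. The planned control rate of 17% is little more than half the 30% given twice elsewhere. PIP-IVF is described as pragmatic with broad inclusion, and nothing in the article says why its control women should do so much worse than the general rate, or why live birth should almost double.

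What is at stake is mainly how a fresh or frozen result will be read. The sample was doubled for those strata, 90% power was chosen explicitly to limit type 2 error, and the Discussion says the procedure can be abandoned if no effect is found. A non-significant result in one stratum would be read as adequately powered when, on the effect the article itself cites, it may not be. The paragraph's own calculation also needs checking, because the stated 90% is the baseline for any such reading.

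**Working it through.** **Inputs.** From the PIP-IVF sample size paragraph: 17% and 33%, two-sided 5%, 90% power, 188 per arm, doubled to 752. From Randomisation: 1:1 allocation. From the Background: RR 1.42 (1.08–1.85) and 30% per cycle. With equal fresh and frozen recruitment, 752 is 376 per stratum, or 188 per arm per stratum and 376 per arm overall. All 840 women give 840/4 = 210 per arm per stratum.

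**Formula** (two proportions, pooled variance under the null, p̄ the mean of p1 and p2):

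n per arm = [1.96·√(2p̄(1−p̄)) + z_power·√(p1(1−p1) + p2(1−p2))]² / (p1−p2)²

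Power = Φ{[|p1−p2|·√n − 1.96·√(2p̄(1−p̄))] / √(p1(1−p1) + p2(1−p2))}

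**Step 1: the plan's own figure.** For 17% versus 33%, p̄ = 0.25, the null term is 1.2002 and the alternative term is 0.6018.

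- 90% power: (1.2002 + 1.2816 × 0.6018)² / 0.16² = 151.8, so 152 per arm (165 with continuity correction).
- 95% power: (1.2002 + 1.6449 × 0.6018)² / 0.16² = 187.4, so 188 per arm.

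The stated 188 is therefore not the 90% number. The unpooled formula (149) and the arcsine formula (151) do not give it either. At 188 per arm, power for 17% versus 33% is 95.1%.

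**Step 2: the planned effect beside the cited one.** 0.33/0.17 = 1.94, against 1.42 (1.08–1.85).

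**Step 3: power at the cited RR.** For a 30% control rate, 0.30 × 1.42 = 42.6%, a difference of 12.6 points. The null term is 1.3329 and the alternative term 0.6742, so at 188 per arm power is Φ[(0.126 × 13.711 − 1.3329)/0.6742] = Φ(0.586) = 72.1%. The same calculation gives:

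| Control | Biopsy | Basis | Per stratum, 188/arm | Per stratum, 210/arm | Overall, 376/arm |
|---|---|---|---|---|---|
| 17% | 33% | plan | 95.1% | 96.8% | 99.9% |
| 30% | 42.6% | RR 1.42 | 72.1% | 76.8% | 95.0% |
| 25% (assumed midpoint) | 35.5% | RR 1.42 | 60.2% | 65.0% | 88.1% |
| 17% | 24.1% | RR 1.42 | 40.2% | 44.0% | 67.9% |
| 30% | 46% | 16 points | 89.5% | 92.5% | 99.5% |

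For 90% power within a stratum at 30% versus 42.6%, 304 per arm would be needed.

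**Step 4: what drives the fall.** The last row moves the control rate to 30% but keeps the planned 16-point difference, and stratum power stays near 90%. That row corresponds to RR 46/30 = 1.53. The drop to 72% therefore comes from replacing the planned difference with RR 1.42, not from the higher control rate alone.

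**The case against.** Several points on the other side are sound.

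- **Different sources.** The 17% and 33%, the RR of 1.42 and the 30% carry three separate citations. A reader might infer that the article contradicts itself or misquotes its source. The documents do not support that, because the cited reviews may pool different trials. What they show is an inconsistency left unexplained.
- **The 30% is a general figure.** It is a per-cycle IVF rate. PIP-IVF counts live birth per woman randomised, from one transfer within a time limit, treats missing outcomes as no live birth, and includes frozen-thaw transfers. The trial's control rate could well be below 30%. This stands, and it is why a range is shown. A lower control rate at RR 1.42 makes power worse, not better.
- **The stratum claim is implied.** No sentence gives 90% power per stratum. It follows from doubling a sample calculated at a stated 90% under equal recruitment, so it is a fair reading, but still an inference.
- **The primary comparison.** A reader might infer that PIP-IVF as a whole is underpowered. At 30% and RR 1.42 it has about 95% power, above the target. It falls to 68% only if the 17% control rate is kept with RR 1.42.
- **The contingency.** All randomised women stay in the denominator, so 210 per arm per stratum is arguable. That gives 77%, before any dilution from failed biopsies or imputed outcomes, and is still short of 90%.
- **188 is generous.** It is, for 17% versus 33%, but the 72% is computed at 188 and already includes that margin.

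**Conclusion.** The point holds as an unreconciled planning assumption together with a misstated power. The planned RR of 1.94 lies outside the interval the article cites, and its 17% control rate sits unexplained beside 30%. At RR 1.42, power is about 40–72% per stratum (188 per arm) and 68–95% overall (376 per arm) for control rates of 17–30%. Independently of that, 188 per arm gives 95%, not 90%, for the article's own 17% versus 33%.

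This rests on a two-sided 5% test of two proportions, equal fresh and frozen recruitment as the article assumes, a within-stratum comparison as in the article's own example, and RR 1.42 applied to both strata. Pairing the 30% with the 1.42 combines two sources and is an assumption of this check. If the true difference is 16 points from a 30% control rate, the strata are powered at about 90% and the shortfall disappears.

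**What to change.** Keep 840 and reword the paragraph.

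1. Correct the power for 17% versus 33% at 188 per arm to about 95%; alternatively, note that 90% needs 152 (165 with continuity correction) and that 188 was retained.
2. Say why the planning rates differ from the RR of 1.42 and the 30% cited elsewhere.
3. Add power at RR 1.42 for control rates of 17–30%: about 68–95% overall and 40–72% per stratum at 188 per arm.
4. Do not present the fresh and frozen strata as powered at 90%, except under the 16-point difference, and name that condition.

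The cost is wording only, with no extra women and no change to the analysis. The downside is that the stated stratum power becomes less favourable, and a null result in either stratum will have to be reported more cautiously.
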